#### Secondary outcomes

Level of performing daily activities resulting from chronic pain will be measured by the Pain Disability Index (PDI) [56], which consists of seven items using an 11-point Likert scale ranging from 0 (no disability) to 10 (total disability). A total score is derived by summing up the item responses, ranging from 0 up to 70, with a higher score indicating more disability [56]. Good psychometric properties of the PDI have been shown and normative data are available [57].

Pain intensity is assessed by a 100-mm Visual Analogue Scale (VAS). The VAS is a common and valid tool for measuring pain intensity [58].

In order to assess the participant’s self-reported main complaints, the Patient Specific Complaints questionnaire (PSC) will be used [59,60]. The participant selects three to five most limited functional activities and rates the difficulty to perform them during the previous week on a 100-mm VAS [60]. It is tested as valid, reliable, and responsive in patients with chronic musculoskeletal pain [61,62].

Drop-out will be registered in the patient registry in the institution. Each patient will be classified as either a participant who has completed the pain rehabilitation program as proposed or who has dropped out prematurely. In addition, the attendance of each treatment session will be assessed. The level of adherence to the pre-treatment intervention (MIP and UC) is computed by dividing the number of the PREPARE sessions that an individual participant actually has attended by the number of two pre-treatment sessions as planned.

Adherence to the rehabilitation treatment is computed by dividing the number of scheduled treatment sessions (which amount is tailored to the participants’ needs) by the actual attended number of visits. This method has been reported extensively in the literature as a measure of adherence to rehabilitation [63].

General self-efficacy is assessed by the Dutch General Self-efficacy questionnaire [64]. Ten items ranging from ‘totally untrue’ up to ‘totally true’ assess coping in general life demands. A confirmatory factors analysis has taken place in elderly [65] showing a good fit.

A disease-specific self-efficacy measure is used, namely the Chronic Pain Self-efficacy Scale (CPSS) consisting of 22 items the three subscales pain management, coping, and physical function. It offers good overall internal consistency and acceptable test-retest reliability [66].

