### Aims

The primary objective of this current project is to study the effectiveness of MI by means of the MIP intervention. The interventions aims at decreasing drop-out rate and increasing adherence to treatment program to reach a high level of societal participation ultimately in patients with non-specific musculoskeletal chronic pain, who have been selected for pain rehabilitation treatment.

The main research questions are:

1. What is the effectiveness of MI-based pre-treatment (MIP) compared to usual care (UC) on the level of participation, treatment drop-out rate, and adherence in patients with chronic non-specific musculoskeletal pain following pain rehabilitation?

2. What is the cost-effectiveness and cost-utility of MIP, compared to UC from a societal perspective?

3. What is the feasibility of the MIP intervention in terms of MI fidelity (process evaluation)?

4. What are experiences of nurses and patients in terms of satisfaction with and barriers of the MIP intervention (process evaluation)?

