### Hypotheses

1a. It is expected that patients’ level of social participation will be higher in the MIP intervention condition compared to the UC after pain rehabilitation treatment and at 6-month follow-up after finishing the rehabilitation treatment.

1b. It is hypothesized that drop-out rates will be lower and adherence to the treatment and the level performing daily activities) will be higher in the MIP condition compared to the UC.

2. It is hypothesized that MIP will be more efficient compared to UC, both in effects as well as utilities.

3. It is hypothesized that the MIP intervention is feasible for the participating nurses and the MI fidelity of the MIP intervention is sufficient.

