#### Effect evaluation

Baseline data will be analyzed to describe the characteristics of all participants and to check for significant imbalances between the two groups. Possible baseline differences between the intervention group and the control group will be tested by an independent samples *t*-test (normal distribution) or Mann–Whitney U tests (non-normal distribution) in the case of continuous variables. In the case of dichotomous variables, a Chi-square test will be used. In case of imbalances in prognostic factors between both randomized groups, an adjustment for those factors will take place. The number of drop-outs and follow-up losses in both groups will be reported based on descriptive data. Differences in primary and secondary outcome measures between MIP and UC will be analyzed using repeated measurements techniques and multilevel analysis. This approach is chosen because repeated measures within individual subjects are taken. A *P* value <0.05 is considered statistically significant. Data will be analyzed according to the intention-to-treat principle. All outcomes will be assessed at each follow-up moment by taking into account a specific a priori hypothesis. Additionally, per protocol analyses will be performed to assess whether protocol deviations have caused bias.

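### The secondary outcome of adherence to rehabilitation is defined as an inverted ratio (scheduled over attended), so higher scores mean poorer attendance and a patient who attends nothing has no score

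*Protocol article*

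**What the plan says.** The Secondary outcomes section of the protocol article defines two adherence measures in consecutive sentences.

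- Pre-treatment (MIP or UC sessions): "dividing the number of the PREPARE sessions that an individual participant actually has attended by the number of two pre-treatment sessions as planned". This is attended over planned.
- Rehabilitation: "Adherence to the rehabilitation treatment is computed by dividing the number of scheduled treatment sessions" (with the remark "which amount is tailored to the participants’ needs") "by the actual attended number of visits". This is scheduled over attended.

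Hypothesis 1b expects "adherence to the treatment and the level performing daily activities) will be higher in the MIP condition", and the Aims section describes the intervention as directed at "decreasing drop-out rate and increasing adherence to treatment program". The Effect evaluation section adds: "Data will be analyzed according to the intention-to-treat principle". Nowhere does the article recode the rehabilitation ratio, say that lower values are better, or assign a value to a patient who attends no session.

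**The concern.** Dividing scheduled by attended gives an index on which the best possible patient has the lowest score and the score climbs without limit as attendance falls. Two outcomes that share the name adherence then point in opposite directions, and one of them also runs against the hypothesis it is meant to test.

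Attendance level is in the trial's title and adherence is in research question 1, so the result will be looked at. If the rule is coded as printed and higher is taken to mean better, a benefit of MIP would be reported as harm. If the sign is noticed and read correctly, two problems remain: the reciprocal scale gives great weight to the poorest attenders, and anyone with no attendance has no value in an analysis meant to follow intention to treat. If the analyst silently turns the ratio over, the analysis departs from the published definition without a record.

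**Working it through.** **The plan's own figures.** The article gives no figure for adherence, so there is none to reproduce. Its only relevant calculation is the sample size on USER-P Satisfaction: a 5-point difference, SD 10, two-sided 5% level and 80% power give 63.8, so 64 per arm by the t-test, 128 in total, and 128 / 0.80 = 160. This reproduces and does not depend on the adherence rule.

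**Step 1: values of the index.** The number of scheduled sessions is individual. I assume 32, from about 13 weeks at 2.5 days a week (13 × 2.5 = 32.5), in line with the duration and intensity given under Current care in pain rehabilitation.

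| Attended of 32 | As written (scheduled/attended) | Attended/scheduled |
|---|---|---|
| 32 | 1 | 1.00 |
| 16 | 2 | 0.50 |
| 8 | 4 | 0.25 |
| 1 | 32 | 0.03 |
| 0 | undefined | 0.00 |

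**Step 2: direction.** Suppose every MIP patient attends 90% and every UC patient 80%. As written, MIP scores 1/0.90 = 1.11 and UC 1/0.80 = 1.25. The better arm has the lower score, opposite to the wording of hypothesis 1b.

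**Step 3: shape, with lower read as better.** Take 30 scheduled sessions.

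- Arm A: nine patients attend 30 and one attends 1. Mean attendance is (9 × 1 + 1/30)/10 = 0.90. The written index averages (9 × 1 + 30)/10 = 3.90.
- Arm B: all attend 20. Mean attendance is 0.67. The written index is 30/20 = 1.50.

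Arm B attends less but looks better even to a reader who knows that lower is good. One patient is responsible.

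**Step 4: effect on a comparison.** All inputs here are assumptions except the 80 per arm: 32 sessions, completers' attendance beta(18, 2) with mean 0.90, drop-outs' attendance uniform over the range shown, Welch t-test, undefined scores removed. Power is the chance of a significant result in favour of MIP, with lower counted as better for the written index. It therefore measures the loss from skew and exclusion, not the reversed sign. Results come from several thousand simulated trials per row and are good to a percentage point or so.

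| Drop-out UC v MIP | Drop-outs attend | Power, attended/scheduled | Power, as written | Means favour wrong arm, attended/scheduled | Means favour wrong arm, as written |
|---|---|---|---|---|---|
| 20% v 10% | 0–60% | about 36% | about 16% | about 5% | about 16% |
| 20% v 10% | 20–80% | about 32% | about 26% | about 6% | about 10% |

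With drop-out of 10% v 5%, power goes from about 19% to 8% if drop-outs attend 0–60%. If they attend 20–80%, it stays between about 13% and 15% under either ratio.

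**Step 5: undefined scores.** When drop-outs attend 0–60%, patients with zero attendance average about 0.6 per 160-patient trial (20% v 10% drop-out) or 0.3 (10% v 5%). When they attend at least 20%, there are none. In these settings most of the damage comes from very low attenders, not from the missing values.

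**The case against.** The strongest reply is that this is a transposed phrase in a condensed article. The neighbouring index is the right way up, the aims and hypothesis speak of more adherence, and the method is described as widely reported. Attendance at each session is recorded, so either ratio can be computed later. I accept that a drafting slip is the likely explanation and that no data are lost. But the article does state the formula, nothing in it corrects the formula, and the cited source for the method is not at hand to settle the matter.

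Four stronger readings might be inferred, and the document does not support them.

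- *That hypothesis 1b as a whole is tested with the wrong sign.* It also covers drop-out and daily activities, which have their own measures, and pre-treatment adherence is correctly defined. No one-sided outcome test is specified: the analysis section gives only a 0.05 threshold, and two-sided testing is stated for the sample size. A reversed scale changes how the estimate is read; it does not bar significance.
- *That the trial loses the patients MIP is meant to help.* Zero attenders are lost from this one index. Drop-out is classified separately for every patient.
- *That the rule mixes units because a visit may hold several sessions.* The article uses the two words loosely, and nothing in it says that one visit contains several counted sessions.
- *That a large loss of power is established.* It rests on drop-outs attending almost nothing and on a Welch test of the raw ratio, and the article specifies neither. Even the correct ratio points the wrong way in some trials. A rank test among those who attend at least once would give the same result under either ratio apart from its sign.

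**Conclusion.** The definition is wrong as written, and the error is confined to one secondary outcome. The inversion, the clash with the adjacent index and with the rehabilitation-adherence part of hypothesis 1b, and the undefined value at zero attendance follow from the wording alone and need no assumption. The distortion of arm means is also certain in kind, because the reciprocal is unbounded and non-linear.

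Its size is not certain. It depends on how much drop-outs attend: power falls by about 20 percentage points in the less favourable 20% v 10% scenario (36 − 16) and by about 6 in the milder one (32 − 26). The excess of trials whose means favour the wrong arm is about 11 points (16 − 5) and 4 points (10 − 6) respectively.

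**What to change.** Replace the sentence with: adherence to the rehabilitation treatment is the number of attended sessions divided by the number of scheduled sessions, ranging from 0 to 1, higher being better, with the value 0 for a patient who has sessions scheduled and attends none. This matches the direction of the pre-treatment index and of hypothesis 1b. While the sentence is open, it would help to say how a patient who never has rehabilitation sessions scheduled is handled, since neither ratio gives that patient a value.

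The cost is one sentence in the protocol or the analysis plan, dated before the outcome data are analysed. It needs no new data, and the sample size does not change.

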**Methods/design:**

Study design: A parallel randomized controlled trial including two interventions: a motivational interviewing pre-pain rehabilitation intervention (MIP) and a usual care (UC) control arm. Follow-up will be 6 months after completion of rehabilitation treatment.

Study population: One hundred and sixty (*n* = 80 per arm) patients with chronic non-specific musculoskeletal pain visiting an outpatient rehabilitation department, who are eligible to participate in an outpatient cognitive behavioral pain rehabilitation program.

Intervention: MIP consists of two sessions to prepare and motivate the patient for pain rehabilitation treatment and its bio psychosocial approach. UC consists of information and education about the etiology and the general rehabilitation approach of chronic pain. Both the MIP and UC contain two sessions of 45 to 60 minutes each.

Objective: The aim of the current study is to evaluate the effectiveness of MIP compared to UC in terms of an increase in the long-term level of societal participation and decrease of drop-out during rehabilitation treatment.

Main study endpoints: Primary outcome is the change in level of participation (according to the ICF-definition: ‘involvement in a life situation’) 6 months after completion of rehabilitation treatment. Secondary outcomes are adherence and treatment drop-out, disability, pain intensity, self-reported main complaints, (pain-specific) self-efficacy, motivation, and quality of life. Costs are calculated including the costs of the pre-treatment intervention, productivity losses, and healthcare utilization. Potential moderators and active ingredients of MI are explored. For the process evaluation, parameters such as MI fidelity, feasibility, and experiences are explored.

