2. Assuming a standard deviation of 10 points in both groups, the standardized effect size, Cohen’s d, is (10–5)/10 = 0.5 indicating a medium additional effect size of the MIP [40].

Assuming power (1-β) of 80%, α = 0.05, two-sided testing, and holding the above mentioned assumptions, would necessitate *n* = 128 participants (*n* = 64 per arm). With an expected total drop-out of 20% (10% drop-out from the study, another 10% drop-out during the usual rehabilitation treatment as our unsystematic registration has shown), *n* = 160 (*n* = 80 per arm) was chosen as the optimal total sample size. Additionally, as the recruitment of 160 participants in the region of South-Limburg/the Netherlands is feasible in a time range of 18 months, we have chosen for this amount of participants.

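### Adherence to rehabilitation is defined upside down (scheduled sessions over attended visits), against the pre-treatment ratio beside it and the direction of hypothesis 1b

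*Protocol article*

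**What the plan says.** The Secondary outcomes section of the protocol article defines two adherence measures in consecutive paragraphs.

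- For the pre-treatment phase, in either arm, the ratio is given as follows: "by dividing the number of the PREPARE sessions that an individual participant actually has attended by the number of two pre-treatment sessions as planned". That is attended over planned.
- For the rehabilitation phase, the ratio is given as follows: "dividing the number of scheduled treatment sessions (which amount is tailored to the participants’ needs) by the actual attended number of visits". That is scheduled over attended.

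The sentence after the second definition supports it by citation: "This method has been reported extensively in the literature as a measure of adherence to rehabilitation". It does not describe the ratio as an index of non-adherence. No other section reverses the scale or says what happens when no visit was attended.

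Hypothesis 1b gives the expected direction. It states that "drop-out rates will be lower and adherence to the treatment" will be higher in the MIP arm. The abstract lists the outcome: "Secondary outcomes are adherence and treatment drop-out, disability, pain intensity". Adherence also appears in main research question 1. For the analysis, the Effect evaluation section states: "Data will be analyzed according to the intention-to-treat principle".

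**The concern.** Two measures with the same name run in opposite directions, and the rehabilitation measure runs against the hypothesis it is meant to test. If MIP improves attendance, the ratio as written falls, so a result in favour of MIP would read as lower adherence.

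Reading the scale backwards does not fully repair this. The reciprocal stretches the low-attendance end, so a mean of scheduled/attended is not a relabelled mean of attended/scheduled. Patients who had sessions scheduled and came to none get no value at all. They are among the patients that an intervention against non-adherence is aimed at, and their number may differ between arms. The sentence at issue is the article's only operational definition of adherence to rehabilitation.

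**Working it through.** The article states no adherence figure, so there is nothing to reproduce. The check evaluates the ratio as written and its reciprocal.

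**Inputs**
- S = sessions scheduled, A = sessions attended. The article gives no value for S and says only that it is tailored. S = 30 is an assumption for illustration. The direction and the division by zero do not depend on it.
- As written: S/A. Reversed, to match the pre-treatment ratio: A/S.

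**Step 1: values for one patient (S = 30 assumed)**

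| Attended A | As written S/A | Reversed A/S |
|---|---|---|
| 30 | 1.00 | 1.00 |
| 27 | 1.11 | 0.90 |
| 24 | 1.25 | 0.80 |
| 15 | 2.00 | 0.50 |
| 3 | 10.0 | 0.10 |
| 1 | 30.0 | 0.03 |
| 0 | undefined | 0.00 |

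The best value as written is 1, and values rise as attendance falls. The largest defined value is S itself, reached at one visit. The pre-treatment ratio gives 2/2 = 1.0, 1/2 = 0.5 and 0/2 = 0, so it rises with attendance and is defined at zero.

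**Step 2: effect on an arm mean.** Assume 90% of an arm attends 27 of 30. The other 10% stop after 3 visits. The 10% share is borrowed from the Sample size section, which expects "another 10% drop-out during the usual rehabilitation treatment as our unsystematic registration has shown"; the attendance counts are assumed.
- If the full programme of 30 still counts as scheduled after stopping: S/A mean = 0.9 × 1.111 + 0.1 × 10 = 1.0 + 1.0 = 2.0, so the 10% supply half of it. A/S mean = 0.9 × 0.90 + 0.1 × 0.10 = 0.82.
- If only the 3 sessions up to stopping count as scheduled, these patients score 3/3 = 1: S/A mean = 0.9 × 1.111 + 0.1 × 1 = 1.1. A/S mean = 0.9 × 0.90 + 0.1 × 1 = 0.91.

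The weight of early stoppers therefore depends on a counting rule that the article does not state.

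**Step 3: can the ranking of arms change?** Take S = 30 throughout. In the first arm half the patients attend 30 and half attend 3. In the second arm all attend 15.
- A/S: (1.00 + 0.10)/2 = 0.55 against 0.50. The first arm is better.
- S/A: (1 + 10)/2 = 5.5 against 2.0. High means poor attendance on this scale, so the first arm is worse.

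The ranking can change even for a reader who knows the scale is inverted. The example is deliberately extreme and shows only that this is possible.

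**The case against.** The strongest reply is that this is a slip in wording. The neighbouring formula and hypothesis 1b both point to attended over scheduled, and an analyst who met values of 1 or more and a division by zero would notice. Attendance is recorded session by session, so nothing is lost at data collection. That is probably right, and it limits the consequences. It does not remove the point, because the sentence is the outcome's definition and is stated wrongly, which differs from leaving a detail to an analysis plan. The citation does not settle it either: the source is not at hand, and the formula still conflicts with the rest of the article.

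Three stronger readings are tempting, and the article does not support them.
- A reader might infer that early drop-outs will dominate the arm means. That holds only if sessions after drop-out count as scheduled; otherwise early stoppers can score close to 1.
- A reader might infer that patients with zero visits are lost to the trial's analysis. They lack a value on this ratio only. Drop-out is classified separately for each patient.
- A reader might infer that the denominator must be fixed at the start of treatment. That is a separate design choice, which the inversion does not require and which may not suit schedules revised during treatment.

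**Conclusion.** The point holds. The rehabilitation adherence ratio is inverted relative to the pre-treatment ratio and to hypothesis 1b. Three consequences follow from the text alone: higher values mean worse attendance; the values do not lie between 0 and 1; and a patient with scheduled sessions and no visits has no value, so an intention-to-treat analysis of this outcome cannot include that patient without a further rule.

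The numerical size of the distortion is not established. The illustrated means (2.0 or 1.1 as written; 0.82 or 0.91 reversed) rest on assumed session counts and on the counting rule after drop-out. A changed ranking of the arms is possible but is not shown to be likely.

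The reach is one secondary outcome, though one named in main research question 1. The primary outcome, the sample size and the drop-out classification do not use this ratio.

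**What to change.** Restate the outcome in one sentence: adherence to rehabilitation is the number of sessions attended divided by the number scheduled, ranging from 0 to 1, higher meaning better adherence, with a patient who attends none of the scheduled sessions scored 0. This gives it the same orientation as the pre-treatment ratio and hypothesis 1b.

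Two optional additions would make the definition complete: when the scheduled number is set, including whether sessions after drop-out count, and how a patient with no sessions ever scheduled is handled, since 0/0 has no value in either form.

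The cost is one corrected sentence, best made before the analysis. The article already plans to record attendance at each session, so no new data are needed.
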